### Intervention

The intervention being evaluated is a cell phone reminder and coordination system, which seeks to coordinate potential recipients of MV with MV opportunities (ie, days in which MV is administered either at their local health center, or at a relevant outreach day). Participants allocated to intervention groups will receive two SMS text reminders in the local language of Portuguese Creole. The first message will be delivered three days before the suitable MV opportunity, and the second will be sent one day before. If the participant is allocated to also receive a phone call, a project worker will call the supplied phone number two days before the MV opportunity.

SMS messages are *active* in the cell phone network for 24 hours, after which the delivery attempt will be considered failed. If the delivery attempt of a first message fails (ie, three days before MV opportunity), the message will be redelivered. If delivery of the second message fails (ie, one day before MV opportunity), it will not be redelivered due to time rendering it irrelevant. If a phone call fails it will be reattempted two times: once on the same day, and a final attempt on the day before MV opportunity. We will register all failed message delivery attempts and account for these in the subsequent analysis.

If several phone numbers are supplied, SMS texts will be sent to all phone numbers. Voice calls will made to one number, and if the call to the first number is not successful, the second number will be attempted, and so on. Voice calls, like the SMS texts, will be made in the Creole language.

If a study participant does not arrive at the MV opportunity, or if the MV opportunity is cancelled or unavailable for any reason, the study participant will receive a new set of messages/voice calls at the next relevant MV opportunity, assuming the child is still eligible (ie, child is 9-12 months of age). The new set of messages will be delivered regardless of whether earlier delivery attempts for the participant failed.

### Follow-Up

When MVs are given in one of the selected health centers, the participants will be registered in the system as having received the vaccination at the given date. The study assistant will also take note of a set of follow-up questions concerning the participants’ motivation for receiving the vaccination as well as a final question as to whether the participant received and understood the text reminder/voice call. The answers to these questions will eliminate the blinding of within the study, since the participants’ answers will reveal their allocation group. In addition, data regarding price of phone call and time spent per phone call will be collected after each call, and analyzed in terms of cost effectiveness.

A qualitative analysis will be done when children reach 13 months of age, for all participants not registered as having received MVs. The analysis will be based on phone interviews to determine the main reasons for not receiving the vaccine, and it will be registered whether the child has received MV at a different location, moved out of the area, or died. All of these participants will be offered MVs for their children.

A selection of participants from each intervention group (n=10-15), who registered their children as having received the MV, will be visited by a study assistant in order to conduct a face-to-face follow-up interview. These interview will focus on the participants’ perception of the intervention message and the overall experience of the intervention. Data collection will rely on digital questionnaires filled out by project assistants during house visits. Difficulty with logistics (ie, locating and visiting the participants) explain the relatively small number of participants selected for this analysis.

### Location and Duration of the Project

In coordination with the Ministry of Health in Guinea-Bissau, three participating health centers will be selected in the aforementioned regions of rural Guinea-Bissau. The centers will be selected based on the size of the health center (ie, the capacity for enrolling enough study participants during a period of six months), distance to neighboring health centers, mobile cell network coverage, and current level of outreach/other studies.

The first component was carried out in the period from October, 2015 to March, 2016. The second component is scheduled to begin in the first quarter of 2016 and end in the third quarter of 2017 (18 months).

### Development of Reminder Content and Timing

In order to assess the intervention context, and determine the optimal timing and content of the messages to be used in the RCT, a qualitative analysis will be conducted. The analysis will be based on field visits in the rural areas to observe the context for the intervention, including the daily routines for mothers with children aged 6-12 months and their usage of mobile technology. In addition to these observations, a number of semistructured qualitative interviews will be conducted to acquire knowledge about what time of day a message would be preferred, and potential cultural barriers preventing the delivery of messages to household members or neighbors (if the mother does not own a phone).

During the interview, the interviewee will be presented with one of three different versions of the intervention message, and asked questions to evaluate their understanding:

1. A very brief description of measles infection and the reasons for vaccination, inspired by a post card MV reminder intervention that was implementing using the *health belief model* [21].

2. A shorter and more imperative message telling the participant to go to the health center to receive the MV.

3. A verbal message read to the interviewee by the interviewer. The messages will be personalized with the baby’s name and the name of the relevant health center.

All of the messages will be presented in two formats, depending on whether the message is to be delivered directly to the participant’s phone or via the phone of a household member/neighbor. The indirect message variants will be evaluated by presenting them to nearby household members and assessing their understanding and willingness to relay the message.

### Technical Implementation

Building on the efforts of UNICEF, the technical aspects of the project will be based on the open source IT system, RapidSMS. This system is well documented, and has previously been applied successfully in comparative interventions in Kenya and Rwanda [10,22]. The system is customizable and will be adapted to the context of this study. The RapidSMS system will generate reports on SMS texts that failed to be delivered to the recipient (eg, due to cell phone being off for longer periods of time, or a changed phone number). These texts will be delivered again. To enable digital data collection using tablets/phones, an adapted version of Open Data Kit will be used.

To enable capacity building, and thus increase the chances of the system being implemented if the intervention is deemed successful, the technical implementation will be done in close coordination with technical personnel from the national Ministry of Health.

## Results

In order to evaluate mHealth as a viable means of increasing MV coverage and timeliness, an RCT will be conducted. The mHealth intervention will be evaluated using the outcomes in Textbox 1.

Outcome measures of the randomized control trial.
**Primary outcome A:**
*MV coverage at 12 months of age.* Difference in MV coverage at 12 months of age between the intervention groups and the control group.
**Secondary outcome B:**
*Timeliness.* Difference in timeliness of MVs administered, measured as median age of vaccinated children.
**Secondary outcome C:**
*Average number of visits* to the health center (with the purpose of receiving MV) needed before MV is successfully administered.

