**Results:**

The study will analyze the efficiency of the intervention by determining its overall effect on MV coverage and timeliness when children reach 12 months of age. The main analysis will be stratified by intervention group, health center, level of education, ethnic group, and role of the person receiving the text messages (eg, mother, father, other family member). Secondary outcomes include the average number of health center visits (with intention to obtain the MV) required before successful administration.

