Measles is the deadliest of all childhood rash/fever illnesses and spreads easily, implying that if the MV coverage is declining [16] there is a significant risk of new measles outbreaks [17]. Recent reports from World Health Organization conclude that increased activities are needed to resume progress towards the 2015 Millennium Development Goals of measles control and elimination [18,19]. In addition, recent studies have lead the Strategic Advisory Group of Experts on Immunization to suggest that MV is associated with possible beneficial effects on all-cause mortality [20]. Interventions that enhance the timeliness and coverage of MV are therefore likely to have a great beneficial impact on child health. Thus, we suggest an mHealth intervention to increase MV coverage by sending vaccination reminders by short message service (SMS) texts to mothers before their child’s scheduled MV. While this intervention aims at increasing awareness amongst mothers, it also presents potential benefits regarding the supply of MVs. Current policies in Guinea-Bissau require a minimum number of children to be present before a vial of vaccine can be opened, and since the health centers typically only administer vaccinations one or two days per week, mothers will often the be sent home and told to return a different day. This intervention has the potential to coordinate the vaccination visits and help ensure that enough children are present for the health centers to open a vial of vaccines on a given day, and ensure that mothers arrive on the correct day at the health centers.

Studies from the INDEPTH Network and GAVI have demonstrated that rural regions have particularly low MV coverage, so this intervention will focus on the rural regions of Tombali, Gabu, and Cacheu in the Southern, Eastern, and Northern Guinea-Bissau, respectively.

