### Objectives

The primary objective of this intervention is to enable a beneficial impact on child health by improving timeliness and coverage of MVs using simple and cost-efficient methods. Specifically, the study aims to investigate whether a mobile phone targeted reminder system can be used in the context of rural Guinea-Bissau, and what effect this intervention can be expected to have, as well as potential obstacles and barriers to implementation.

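### Secondary outcome C averages visits only over vaccinated children, so a difference between arms mixes visit burden with who persists to vaccination and may point either way

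*Protocol article*

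**What the plan says.** All places are in the protocol article.

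- **Textbox 1, Secondary outcome C:** the average number of visits to the health center ("with the purpose of receiving MV) needed before MV is successfully administered"). The Abstract (Results) has the same endpoint: "Secondary outcomes include the average number of health center visits (with intention to obtain the MV) required before successful administration".
- **Introduction, Background:** "Current policies in Guinea-Bissau require a minimum number of children to be present before a vial of vaccine can be opened", and mothers will often "be sent home and told to return a different day". The reminders might "help ensure that enough children are present for the health centers to open a vial of vaccines on a given day", and might bring mothers on the correct day. No rate of failed visits is given.
- **Intervention:** after a missed or cancelled vaccination opportunity, an intervention participant gets a new set of messages or calls while the child is 9 to 12 months old. The control arm gets none.
- **Follow-Up:** "When MVs are given in one of the selected health centers, the participants will be registered in the system as having received the vaccination", with follow-up questions asked then. Children not registered as vaccinated are covered by a phone interview at 13 months on main reasons, vaccination elsewhere, moving and death. No count of unsuccessful visits is described for either group.
- **Sample Size Calculations:** coverage of about 75% in control and at least 85% in each intervention arm.
- **Statistical Analysis:** methods are given for coverage and timeliness. Nothing is said on unvaccinated children in outcome C.

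**The concern.** Outcome C is the only quantitative outcome in Textbox 1 that deals with wasted visits. Under both wordings it is conditional on a post-randomization event, successful vaccination, which is the primary outcome. Randomization does not protect a comparison within that subset.

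The selection also has a plausible route. A reminded mother who was sent home is prompted again, may return, and then enters C with a high count. A control mother with the same failed visits who does not return drops out of C. Reminders may equally bring in mothers who would never have come, and these enter with a low count. The two routes push C in opposite directions, and C cannot tell them apart. At stake is how a secondary result is read: a program that raises coverage could be reported as costing mothers more trips, or a real saving in trips could be missed.

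**Working it through.** **The plan's figures.** The plan states no figure for outcome C. Its 75% and 85% are the rates behind its sample size, which reproduces. With a two-sided 5% level and 80% power, two proportions need 250 per arm uncorrected and 270 with continuity correction, as stated. Then 270/(1 − 0.18) = 330, within the stated 15-20% loss.

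**Share left out of C.** Control 1 − 0.75 = 25%, or 82.5 of 330. Intervention 1 − 0.85 = 15%, or 49.5 of 330. Not all of these were sent home: some never attended, moved, died or were vaccinated elsewhere.

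**Illustration per 100 enrolled.** Visit counts are assumed, and the successful visit is counted. In control, 75 are vaccinated at a mean of 1.5 visits (112.5 visits), 12.5 give up after two failed visits (25 visits) and 12.5 never come. In each scenario 85 are vaccinated.

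1. Ten who would have given up return and are vaccinated at visit 3. Vaccinated: 112.5 + 30 = 142.5 visits. Unvaccinated: 2.5 × 2 = 5.
2. Ten who would never have come are vaccinated at their first visit. Vaccinated: 112.5 + 10 = 122.5. Unvaccinated: 25.
3. As scenario 1, but the other 75 average 1.3 visits because they come on the right day. Vaccinated: 97.5 + 30 = 127.5. Unvaccinated: 5.

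| | C as written | All visits per vaccination | Failed visits per enrolled child |
|---|---|---|---|
| Control | 112.5/75 = 1.50 | 137.5/75 = 1.83 | (137.5 − 75)/100 = 0.625 |
| Scenario 1 | 142.5/85 = 1.68 | 147.5/85 = 1.74 | (147.5 − 85)/100 = 0.625 |
| Scenario 2 | 122.5/85 = 1.44 | 147.5/85 = 1.74 | (147.5 − 85)/100 = 0.625 |
| Scenario 3 | 127.5/85 = 1.50 | 132.5/85 = 1.56 | (132.5 − 85)/100 = 0.475 |

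Scenarios 1 and 2 have the same total visits and the same vaccinations, yet C lies above control in one and below it in the other. In scenario 3, C shows no difference although both other measures improve.

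**Second check with a simple visit model.** Let a be the share who attend at least once, q the chance that a visit ends in vaccination, and r the chance of returning after being sent home. All three are assumed. With D = 1 − (1 − q)r:

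- coverage = aq/D
- C = 1/D
- all visits per vaccination = 1/q
- failed visits per enrolled child = a(1 − q)/D

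| a = 0.95 | Coverage | C | Visits per vaccination | Failed per enrolled |
|---|---|---|---|---|
| Control: q 0.60, r 0.60 | 75% | 1.32 | 1.67 | 0.50 |
| Return only: q 0.60, r 0.824 | 85% | 1.49 | 1.67 | 0.57 |
| Return and success: q 0.65, r 0.824 | 87% | 1.41 | 1.54 | 0.47 |
| Success only: q 0.77, r 0.60 | 85% | 1.16 | 1.30 | 0.25 |

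In the third row both burden measures fall while C rises. In the fourth row C moves the right way. Over the combinations of q (0.5 to 0.8) and r (0.4 to 0.7) where 85% could be reached through return alone, C rose by 0.145 to 0.205 visits with q unchanged. It rose by 0.08 to 0.09 with q also raised by 0.05. Other combinations could not reach 85% that way.

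**The case against.** The strongest case on the other side has five parts.

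- **The wrong direction is assumed.** This is largely right. It needs reminders to act mainly by bringing back mothers who were sent home. Scenario 2 and the success-only row show no such reversal. A reader might infer that C is bound to make a working intervention look worse. The documents give no visit data and do not support that.
- **Mothers who gave up are not lost to the trial.** This is right. They count as unvaccinated in outcome A, whose denominator is all children enrolled, and being sent home may be given as a reason in outcome F. A reader might infer that they count nowhere. What is missing is their failed visits, which enter no visit count.
- **The barriers objective is not left unanswered.** This is right. Objectives refers to the reminder system when it adds "as well as potential obstacles and barriers to implementation". A reader might tie this to the vial-opening rule, but the text does not, and it does not assign that aim to outcome C. Background also presents better supply as a possible further benefit.
- **C has no stated test.** Outcomes A and B are worded as differences, and C as an average. But the introduction to Textbox 1 says the intervention will be evaluated by these outcomes, so a comparison by arm is the natural reading.
- **The article is condensed, and visit forms may exist elsewhere.** That is possible, and it is why the missing visit field is not the main point. The definition itself is stated twice and ends at successful vaccination both times.

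**Conclusion.** The point holds as one about the definition of a secondary outcome. C is conditional on the event the intervention is meant to change, so a difference between arms mixes visit burden with who persists to vaccination. It cannot be read as burden in either direction. The excluded shares, 25% and 15%, rest on the plan's own coverage rates. The shifts in C (from 1.50 to 1.68, 1.44 or 1.50; from 1.32 to 1.49, 1.41 or 1.16) rest wholly on assumed visit behavior and show only what is possible. Whether the successful visit is counted does not matter here: leaving it out lowers every value of C by one and changes no difference. The primary outcome is not affected.

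**What to change.** Define outcome C by arm over all enrolled children, with two figures reported together:

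1. visits made to obtain the vaccine that ended without it, per enrolled child, up to 366 days of age;
2. total visits made to obtain the vaccine, divided by the number of children vaccinated.

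Both are needed. Figure 1 can rise simply because mothers persist (0.50 to 0.57 in the return-only row), which is a real burden but has to be read beside the vaccinations gained. Keep the present mean among vaccinated children as description only.

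To collect the count, put the same question on earlier visits for the vaccine into the follow-up questionnaire at vaccination and into the 13-month phone interview already planned for unregistered children. Study assistants may also log study children who are sent home on days they already attend. Logging every such child on all days, including non-vaccination and outreach days, could need extra staff time and should not be required.

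The cost is a change of wording and one question asked at two existing contacts. The downsides are recall error, which may differ between the two time points and hence by vaccination status, and missing counts for mothers not reached by phone. The number of missing counts should be reported by arm.

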**Secondary outcome D:**
*Analysis of context and evaluation* of the different intervention messages.
**Secondary outcome E:**
*Cost/benefit analysis of verbal telephone messages versus SMS messages.* The costs in terms of time spent (voice calls), SMS fees, and technical setup will be evaluated against the observed behavior change.
**Secondary outcome F:**
*Reasons for nonvaccination.* Qualitative study of the main reasons for noncompliance with the Expanded Program on Immunization, among participants whose children have not received the MV before 13 months of age.
**Secondary outcome G:**
*Effect of collecting multiple phone numbers.* Analysis of whether the number of phone numbers collected per participant influences the success rate of the intervention.
**Secondary outcome H:**
*Qualitative evaluation* of the participants’ perception of the intervention message and overall experience of the intervention.

### Safety & Ethics

#### Ethical Considerations

One of the key challenges in relation to mHealth is the issue of privacy and data security [23], especially when potentially stigmatizing diseases or substance abuse could be disclosed if family members or others see the text messages, or gain access to the phone used for the intervention [24]. This issue becomes all the more relevant since we have chosen to include mothers, some of whom do not have their own phones, but only have access to shared phones. However, it is our judgment that vaccination reminders do not represent any risk of unwanted disclosure. In addition, a recent study from Argentina concluded that 96% of the study participants (pregnant women attending antenatal care) responded that they would like to receive text messages and phone calls [25]. We have chosen to include participants who do not have their own private phones in an attempt to avoid adding further to the *digital divide* (ie, social inequality due to lack of access to and/or knowledge of information and communication technology).

Another ethical consideration is how to embrace illiteracy/multiple spoken languages without adding to cultural divides or discrimination against certain population segments or ethnic groups. Culture-specific wording of messages is also important, in order to avoid unintended negative effects [26]. At the time of enrollment, trained health workers will describe the study in detail to the potential participants, and assess their understanding in order to obtain their informed consent. All information will be available in Creole (the primary spoken language of Bissau).

To avoid sending SMS reminders to participants who have died or moved out of the study area, or those whose children have died or received the vaccine ahead of schedule, follow-up will be done to the extent possible at the health facilities. It is likely that some of these events will go unnoticed, potentially resulting in inappropriate messages being sent. This problem does not differ from current practices of the Health and Demographic Surveillance System routines, in which families are occasionally asked about deceased members of the household. The possibility of receiving a message regarding a deceased child will furthermore be explained during the informed consent phase.

#### Registration and Ethical Approvals

This project has obtained the approval of the ethical committee of Guinea-Bissau as well as a guiding statement from the ethical body Udlandsudvalget in Denmark. The project has also registered with clinicaltrials.gov (reg.no. NCT02662595).

### Data Management & Statistical Analysis

#### Data Management

The data will be collected using digital questionnaires and stored in a protected database. The data will not be shared with people or organizations outside of the Bandim Health Project, unless proper authorizations are obtained from the ethical committee in Guinea-Bissau. However, the collected data might be made available to an external project group as part of ongoing monitoring and evaluation efforts.

